#### Transplant free survival at one year

Liver transplants are identified on the SAE form. If a participant has a liver transplant indicated via the CTCAE category on the SAE form then the participant is termed as having "had a liver transplant". Participants which do not fulfil this criteria will be termed as having "not had a liver transplant".

If a participant has "had a liver transplant" then their time till transplant will be defined as the number of days from the date of randomisation till the date of transplant (indicated by the date of onset on the SAE form). If the time till transplant is  $\leq 365$  days the question "Transplant free survival at 1 year?" is answered "no". If the time till transplant is  $> 365$  the question

"Transplant free survival at 1 year?" is answered "yes".

If a participant is "transplant free" then their time till transplant will be the number of days from the date of randomisation to the date last known to be transplant free. This will be determined by the completion date of the most recent trial form received. If the censored time is  $> 365$  then the question "Transplant free survival at 1 year?" is answered "yes". If the censored time  $\leq 365$  days but the follow-up CRF has been completed within the window of assessment (no earlier than 351 days from randomisation) then "Transplant free survival at 1 year?" is still answered "yes". If the censored time is  $\leq 365$  and the 12-month follow-up CRF has not been returned then there is not complete information regarding transplant free survival within 1 year for this participant. Therefore, the answer to "Transplant free survival at 1 year?" is considered to be missing.

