### **4.4. Secondary outcome measures**

The secondary outcomes are as follows:

- Time to first variceal bleed in days (from randomisation).
- Mortality at one year (from randomisation):
  - All-cause mortality
  - Liver related mortality
  - Cardiovascular mortality.
- Transplant free survival at one year (from randomisation).
- Adverse events related to treatment (up to 12 months after randomisation):
  - Dysphagia requiring discontinuation of treatment
  - Symptomatic hypotension requiring change in treatment
  - Dyspnoea
  - Gastrointestinal upset.
- Other complications of cirrhosis:
  - New onset ascites confirmed clinically or on imaging and graded as per ICA recommendations.
  - New onset encephalopathy defined using West Haven Criteria.
  - Spontaneous bacterial peritonitis
  - Hepatocellular carcinoma
  - Any renal dysfunction as per International Club of Ascites – Acute Kidney Injury (ICA-AKI) definitions.
- Health-related quality of life (EQ-5D-5L) from randomisation to six and 12 months.
- Use of healthcare resources, costs and cost-effectiveness based on the outcomes of cost per variceal bleeding avoided within one year of randomisation, cost per Quality-adjusted Life-year (QALY) estimated using the EQ-5D-5L, and cost per death avoided at 1 year.
- Participant preference (via qualitative interviews in the pilot study). This qualitative data will complement quantitative outcome assessment.
- Use of alternative therapies.
- Crossover therapies.

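### The derivation of transplant free survival at one year never counts death as a failure, so a participant who dies untransplanted is coded missing or, in some cases, 'yes'

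*SAP*

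**What the plan says.** SAP section 4.4 lists transplant free survival at one year from randomisation as a secondary outcome. The operative definition is in section 9.4 under the same name.

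- **Classification.** Only transplant is used: "If a participant has a liver transplant indicated via the CTCAE category on the SAE form then the participant is termed as having" had one. All others form a single class, with no split into alive and dead.
- **Transplanted.** The answer is 'no' if the transplant is by day 365, and 'yes' if later.
- **Not transplanted.** Time runs as "the number of days from the date of randomisation to the date last known to be transplant free". On the source of that date the SAP says: "This will be determined by the completion date of the most recent trial form received". The answer is 'yes' if this time exceeds 365 days, or if it does not but the follow-up CRF was completed on day 351 or later.
- **Missing.** If the time is 365 days or less and the "12-month follow-up CRF has not been returned then there is not complete information regarding transplant free survival within 1 year for this participant", the answer is missing.

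Death is not mentioned in this derivation. The derivation just before it, for all-cause mortality, first separates dead from alive using the death variable on the SAE form, and applies form-date rules only to the living. Section 9.6 says that transplant free survival is analysed like all-cause mortality (log-binomial risk ratio and risk difference). It restricts secondary outcomes to participants with data at the time point.

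**The concern.** Survival free of transplant is a composite: a participant fails by dying or by being transplanted. The written rule has only the second kind of failure. A participant known to have died untransplanted has a fully known outcome, yet the rule either calls the information incomplete or lets the date of a later form produce a 'yes'.

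Two things are at stake. The percentage reported as transplant free survival would be too high in both arms. A mortality difference between carvedilol and banding, which this outcome should pick up, would be largely removed from it. Section 9.10 limits sensitivity analyses to the primary outcome, so no planned analysis would expose the problem.

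There is also a smaller gap. The 'missing' rule requires that the 12-month CRF was not returned, and the 'yes' rule requires completion on day 351 or later. An untransplanted participant whose 12-month CRF came before day 351, with no form dated after day 365, meets neither.

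**Working it through.** The SAP states no figure for this outcome, so there is nothing to reproduce. The check has two parts.

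**1. The rule applied to example participants, none transplanted** (SAE forms counted as trial forms)

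| Participant | Branch met | Code as written | Correct code |
|---|---|---|---|
| Dies day 200, last form day 205, no 12-month CRF | time ≤365, CRF not returned | missing | no |
| Dies day 350, SAE form completed day 370 | time >365 | yes | no |
| Dies day 200, 12-month CRF completed from notes day 355 | CRF on day 351 or later | yes | no |
| Alive, 12-month CRF day 320, no later form | none | undefined | needs a rule |

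No branch gives 'no' for a death without transplant. Deaths that follow a transplant by day 365 are already 'no', so the error is confined to deaths without a prior transplant.

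The last row can occur: day 320 is 365 − 320 = 45 days early, inside the two months either side that Appendix C allows for the 12-month visit. The mortality rule covers this case, because its 'missing' branch applies when the CRF was not returned inside the assessment window. The transplant rule lacks that qualifier.

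**2. Size, under assumed rates**

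The SAP gives no expected transplant or death rate for this population, so these inputs are assumptions. Let *t* be the proportion transplanted by day 365 and *d* the proportion dying untransplanted by then, with no other missing data.

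- True transplant free survival: 1 − t − d
- As coded, all such deaths missing: (1 − t − d)/(1 − d) = 1 − t/(1 − d)
- As coded, all such deaths 'yes': 1 − t

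*Example A: t = 3% in both arms, d = 8% against 12%.*

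| | Arm 1 | Arm 2 | Difference | Failure risk ratio |
|---|---|---|---|---|
| True | 89% | 85% | 4.0 points | 11/15 = 0.73 |
| Deaths missing | 89/92 = 96.7% | 85/88 = 96.6% | 0.1 points | (3/92)/(3/88) = 0.96 |
| Deaths 'yes' | 97% | 97% | 0 | 3/3 = 1.00 |

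*Example B: t = 2%, d = 10% against 15%.* True survival is 88% against 83%, with failure risk ratio 12/17 = 0.71. With deaths missing it is 88/90 = 97.8% against 83/85 = 97.6%, with ratio (2/90)/(2/85) = 0.94. With deaths coded 'yes' it is 98% in both arms, with ratio 1.00.

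*Range of death rates, t = 2%.*

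| d | True | Deaths missing | Deaths 'yes' |
|---|---|---|---|
| 5% | 93% | 93/95 = 97.9% | 98% |
| 10% | 88% | 88/90 = 97.8% | 98% |
| 15% | 83% | 83/85 = 97.6% | 98% |
| 20% | 78% | 78/80 = 97.5% | 98% |

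Over this range true survival falls by 15 points, while the coded value moves by less than half a point.

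**The case against.** The best case on the other side is that this is a drafting slip with limited reach. The name of the outcome shows that a composite was intended. It is one of many secondary outcomes and does not enter the sample size. All-cause, liver-related and cardiovascular mortality each have their own analysis. All of that is true. It limits the consequence but leaves the derivation as it is, and the derivation is what would be programmed. The statement in section 9.6 that the outcome is analysed like mortality sets the model, not who counts as a failure.

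A second argument turns on terms. Section 9.4 first defines a class without a liver transplant, then gives the form-date rules for participants who are 'transplant free', which it does not define. If that phrase meant alive and untransplanted, deaths would not be coded 'yes' or missing; they would have no code at all. That is still a defect, with the same remedy.

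Three stronger readings are tempting and are not supported:

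- *That the dead are generally reported as survivors.* A 'yes' needs a form after day 365, or a follow-up CRF on day 351 or later, for someone who has died. The SAP does not rule this out, but gives nothing on how often it would happen. Missing is the likelier result for most deaths.
- *That the trial would lose a mortality difference.* It would be lost largely from this outcome only. Where mortality is similar in the two arms, the comparison would change little, although both percentages would still be too high.
- *That any early 12-month CRF falls through the rules.* A transplant by day 365, or any later form dated after day 365, still places the participant in a branch.

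**Conclusion.** The point holds. As written, no participant who dies untransplanted by day 365 can be coded as a failure, and no other section of the SAP repairs this. That conclusion comes from the text and needs no assumed rate.

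The direction of the error in the percentage is also certain: it is too high whenever such deaths occur and some participants are transplanted or the deaths are coded 'yes'. Its size depends on death and transplant rates that the SAP does not give. In the illustrations, a true difference of 4 to 5 points shrinks to about 0.1 points if all deaths go missing, and to zero if all are coded 'yes'. The actual split between the two codes cannot be known from the document.

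The rule should be corrected before the outcome is derived. The gap for early 12-month CRFs is a minor wording matter that can be closed at the same time.

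**What to change.** In section 9.4, under transplant free survival at one year:

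1. Answer 'no' if either death from any cause (the SAE form's death variable and the date of death, as in the all-cause mortality derivation) or liver transplant occurs on or before day 365.
2. Apply the last-form-date and day-351 rules only to participants not recorded as dead or transplanted by day 365. The result is 'yes' or missing, as for mortality. The outcome is binary and analysed by log-binomial regression, so the residual category is missing, not censored.
3. Add to the 'missing' rule the mortality derivation's qualifier that the 12-month CRF was not returned inside the assessment window. State that the window meant is the one starting at day 351, since Appendix C gives two months either side for the visit. An untransplanted participant with an earlier CRF and no form after day 365 then has a defined code.

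The cost is a short SAP amendment and the matching change in the derivation program. Death, date of death and transplant are already used in the SAP's own derivations, so no new data are needed.

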#### EQ-5D-5L

EQ-5D-5L is a 6-item questionnaire consisting of five multiple-choice questions and one visual analogue scale. The five multiple-choice questions concern different aspects of health (mobility, self-care, usual activities, pain/discomfort and anxiety/depression) and each require the participant to select one of five ordered responses to indicate their level of problems with each aspect. The permitted responses are chosen from one of the following: no problems=1, slight problems=2, moderate problem=3, severe problems=4, extreme problems/unable to perform activity=5. The numbers assigned to each state are then converted using the official scoring method to obtain a score. The numbers 1-5 assigned to each state have no arithmetic properties and will not be used as cardinal scores themselves. The visual analogue scale is numbered from 0 to 100, where 0 indicates the worst health a participant can imagine and 100 indicates the best health a participant can imagine. Higher scores are better for both the multiple-choice final score and the visual analogue scale. Due to the subjective nature of a questionnaire, EQ-5D responses outside of the scheduled window of assessment ( $\pm 2$  months) will be removed in a sensitivity analysis.

#### **Other Measures**

##### Age at randomisation

Calculated as the number of years from the year of birth to the year of randomisation, with a subtraction of 1 if the birthday has not been yet reached in the randomisation year.

##### Body Mass Index (BMI)

Calculated using the weight and height of a participant obtained from clinical records via the following formula;  $BMI = \text{Weight (kg)} / \text{Height (m)}^2$

##### MELD Score

The MELD score is calculated via a formula involving serum creatinine (mg/dL), serum bilirubin (mg/dL) and INR which are all components of standard care blood test results. Where INR is

not available, it will be calculated using prothrombin time:  $INR = PT_{patient}/PT_{control}$ . The data will be collected on the baseline and follow-up CRFs. Serum creatinine and serum bilirubin are recorded in  $\mu\text{mol/L}$  on the CRFs. The following conversion is used to obtain values for these measures in  $\text{mg/dL}$ :

Serum creatinine ( $\text{mg/dL}$ ) =  $0.01131222 \times \text{Serum creatinine } (\mu\text{mol/L})$

Serum bilirubin ( $\text{mg/dL}$ ) =  $0.01131222 \times \text{Serum bilirubin } (\mu\text{mol/L})$

These values can then be used directly in the MELD score formula as follows:

MELD Score =  $10 \times [0.957 \times \ln(\max(1, \min(\text{serum creatinine } (\text{mg/dL}), 4)))$   
 $+ 0.378 \times \ln(\max(1, \text{serum bilirubin } (\text{mg/dL})))$   
 $+ 1.120 \times \ln(\max(1, INR)) + 0.643]$

Where the  $\ln()$  function takes the natural logarithm, the  $\max(x, y)$  function takes the larger of the values  $x$  and  $y$  and the  $\min(x, y)$  function takes the smaller of the values  $x$  and  $y$ . The MELD score should then be rounded to the nearest integer.

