#### Child-Pugh Score

The Child-Pugh score is calculated from blood test results, presence of ascites and presence of encephalopathy all of which are recorded on the baseline and follow-up CRFs. The blood test results required are serum albumin ( $\text{mg/dL}$ ), INR and serum bilirubin ( $\text{mg/dL}$ ). Where INR is not available, it will be calculated using prothrombin time:  $INR = PT_{patient}/PT_{control}$ . Serum albumin is recorded in  $\text{g/L}$  on the CRFs and serum bilirubin is recorded in  $\mu\text{mol/L}$  on the CRFs. The following conversions are performed before use in the Child-Pugh score formula:

Serum albumin ( $\text{mg/dL}$ ) =  $100 \times \text{Serum albumin } (\mu\text{mol/L})$

Serum bilirubin ( $\text{mg/dL}$ ) =  $0.01131222 \times \text{Serum bilirubin } (\mu\text{mol/L})$

The five constituent variables are each separately categorised into one of three levels (1, 2, 3) in the following way:

|                                    | Score  |                      |                      |
|------------------------------------|--------|----------------------|----------------------|
|                                    | 1      | 2                    | 3                    |
|                                    |        |                      |                      |
| Serum albumin ( $\text{mg/dL}$ )   | >3.5   | 2.8-3.5              | <2.8                 |
| INR                                | <1.7   | 1.7-2.3              | >2.3                 |
| Serum bilirubin ( $\text{mg/dL}$ ) | <2     | 2-3                  | >3                   |
| Ascites                            | Absent | Slight               | Moderate/Severe      |
| Encephalopathy                     | Absent | Moderate(Stage I-II) | Severe(Stage III-IV) |

The Child-Pugh score is then calculated for each participant by adding the five scored

components:

Child-Pugh Score = Serum albumin score + INR score + Serum bilirubin score  
+ Ascites score + Encephalopathy score.

The minimum possible score is 5 and the maximum possible score is 15.

The Child-Pugh score is then converted into the Child-Pugh grade as follows:

| Child-Pugh Score | Child-Pugh Grade |
|-------------------------|-------------------------|
| 5 to 6                  | A                       |
| 7 to 9                  | B                       |
| 10 to 15                | C                       |

*Time to eradication of varices (VBL participants only)*

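### SAP section 9.4 converts bilirubin with the creatinine factor, so converted bilirubin is about 5.2 times too low and MELD and Child-Pugh are understated

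*SAP*

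**What the plan says.** Under Other Measures in section 9.4, the MELD Score entry gives the units on the CRF: "Serum creatinine and serum bilirubin are recorded in" µmol/L. It continues "The following conversion is used to obtain values for these measures in" mg/dL, and prints two equations. Each multiplies the recorded value by 0.01131222, one for creatinine and one for bilirubin. It then says "These values can then be used directly in the MELD score formula as follows". In that formula bilirubin is floored at 1 mg/dL, its natural log is multiplied by 0.378, and the sum is multiplied by 10.

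The Child-Pugh entry says "The following conversions are performed before use in the Child-Pugh score formula" and again multiplies bilirubin in µmol/L by 0.01131222. The result is scored 1 below 2 mg/dL, 2 from 2 to 3 mg/dL, and 3 above 3 mg/dL.

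The SAP contains no other bilirubin conversion. Section 9.4 opens by saying that the Trial Statistician derives all responses from the raw data, so the SAP describes no separately calculated score that would expose the error.

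**The concern.** Converting a molar concentration to a mass concentration depends on the molar mass of the substance. Creatinine and bilirubin are different molecules of very different size, so an identical factor to seven significant figures must be wrong for at least one of them. The creatinine factor appears to have been copied to the bilirubin line and then carried into Child-Pugh.

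A programmer who follows the SAP exactly would code the error. It always acts in one direction, towards milder disease, and affects only participants with raised bilirubin, so it does not average out. The trial enrols patients with cirrhosis, and these two scores are the SAP's defined summaries of liver disease severity, built from baseline and follow-up CRF data. Readers judging to whom the results apply would be given wrong figures.

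**Working it through.** **Inputs from the SAP (section 9.4).** CRF unit µmol/L for both analytes; factor 0.01131222 for both; MELD bilirubin term 10 × 0.378 × ln(max(1, bilirubin in mg/dL)); Child-Pugh cut-points 2 and 3 mg/dL.

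**Assumption from outside the SAP.** Molar masses, which are physical constants: creatinine 113.12 g/mol; bilirubin 584.66 to 584.67 g/mol, or the usual rounded equivalence 1 mg/dL = 17.1 µmol/L.

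**Formula.** 1 µmol/L of a substance of molar mass M g/mol is M µg/L, which is M/10,000 mg/dL.

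**Step 1: the printed factor.** For creatinine, 113.12/10,000 = 0.011312, and 1/88.4 = 0.01131222. The printed figure reproduces. For bilirubin, 584.66/10,000 = 0.058466, and 1/17.1 = 0.05848. The printed figure does not reproduce; it implies a molar mass of 0.01131222 × 10,000 = 113.12 g/mol, which is that of creatinine.

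**Step 2: size of the error in converted bilirubin.** 0.058466/0.01131222 = 5.168; with 1/17.1 the ratio is 5.170. The range of constants makes no practical difference.

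**Step 3: MELD.** The 1 mg/dL floor should lift at 17.1 µmol/L. With the printed factor it lifts at 1/0.01131222 = 88.4 µmol/L, so every value up to 88.4 contributes nothing. The shortfall before rounding is:

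- at or below 17.1 µmol/L: 0
- at 34.2 µmol/L (truly 2 mg/dL, converted to 0.39): 3.78 × ln 2 = 2.62
- at 51.3 µmol/L (truly 3 mg/dL, converted to 0.58): 3.78 × ln 3 = 4.15
- at 88.4 µmol/L and above: 3.78 × ln 5.17 = 6.21, the maximum

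**Step 4: Child-Pugh.** The cut-points in µmol/L become 2/0.01131222 = 176.8 and 3/0.01131222 = 265.2. They should be 2/0.058466 = 34.2 and 3/0.058466 = 51.3. The bilirubin component is too low by 1 point between about 34 and 51 µmol/L, by 2 between about 51 and 177, and by 1 between about 177 and 265. It is correct below 34 and above 265.

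**Step 5: worked values (bilirubin factor 0.058466).**

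| Bilirubin, µmol/L | mg/dL, SAP factor | mg/dL, bilirubin factor | MELD shortfall | Child-Pugh points, SAP | Child-Pugh points, correct |
|---|---|---|---|---|---|
| 17.1 | 0.193 | 1.000 | 0 | 1 | 1 |
| 30 | 0.339 | 1.754 | 2.12 | 1 | 1 |
| 40 | 0.452 | 2.339 | 3.21 | 1 | 2 |
| 60 | 0.679 | 3.508 | 4.74 | 1 | 3 |
| 150 | 1.697 | 8.770 | 6.21 | 1 | 3 |
| 200 | 2.262 | 11.693 | 6.21 | 2 | 3 |
| 300 | 3.394 | 17.540 | 6.21 | 3 | 3 |

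**Step 6: effect on grade.** Take a bilirubin of 60 µmol/L with the other four components scoring 1 each. The correct total is 3 + 4 = 7, grade B. The SAP gives 1 + 4 = 5, grade A.

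**The case against.** The strongest reply concerns reach. MELD and Child-Pugh are not the primary outcome (section 4.3), listed secondary outcomes (4.4), minimisation factors (4.6, where decompensation means ascites or encephalopathy), named adjustment covariates (9.1), subgroup variables (9.9) or part of a sensitivity analysis (9.10). Data outside the pre-specified outcomes receive simple summaries by group (9.7), and baseline data are not tested (6.2). The same wrong formula applies to both arms, and nothing in the SAP shows that it would distort the treatment comparison. The raw µmol/L values are on the CRFs, so the scores can be recomputed at any time and no data are lost. All of this stands. It limits the damage to the description of the population; it does not make the conversion right.

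Three limits on size also stand. The 5.17-fold error is in converted bilirubin, not in the scores. The MELD differences are before rounding to an integer. The share of participants affected cannot be worked out from the SAP.

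Finally, bilirubin is not the only unit problem in the Child-Pugh entry. Albumin is multiplied by 100 to give mg/dL and then compared with 2.8 and 3.5, so 30 g/L becomes 3,000 and, read literally, scores 1, as would any albumin above 3.5/100 = 0.035 g/L. Its conversion line also labels the input µmol/L, although the text gives g/L. That is a separate error, but it means that correcting bilirubin alone does not restore the Child-Pugh score.

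**Conclusion.** The concern holds. The bilirubin conversion is wrong as written in both places, and nothing else in the SAP corrects it. Converted bilirubin is too low by a factor of 5.17. MELD is too low by 0 to 6.2 points before rounding, and the Child-Pugh total by 0 to 2 points through its bilirubin component, enough to move a participant from grade B to grade A. The only outside input is the molar mass of bilirubin, and the result is stable (5.168 to 5.170) over the usual values. The consequence is misreported disease severity at baseline and follow-up; the primary analysis and the listed secondary analyses are unaffected. It must be corrected because it is a definite error in a prescribed derivation that would put wrong figures in the report.

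**What to change.** In the MELD Score and Child-Pugh Score entries of section 9.4, replace the bilirubin factor by 1/17.1 = 0.0585 mg/dL per µmol/L. Leave the creatinine factor at 0.01131222. Correct the code to match, and test it on hand-calculated cases on both sides of 17.1, 34.2 and 51.3 µmol/L. Recompute any scores already produced with the printed factor.

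The cost is a two-line SAP correction and the matching code change, with no new data. Settle the albumin units in the Child-Pugh entry in the same amendment, since that score stays wrong until both are corrected.
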